#### 2.2.4. Sample Size Calculation

Because there is no preceding study to evaluate the effectiveness of EA for PSUI using the Total Urgency and Frequency Score (TUFS), with a control of any sham devices, we reviewed a statistical study on the appropriate group size for a pilot study. One study suggested that at least 12 participants should be recruited in each group to conduct a pilot trial [14], and another suggested that an increase in size from 12 to 18 or 24 narrowed the confidence interval [15]. Accordingly, we decided that 18 participants per group would be adequate. Therefore, with anticipated dropout rates of 10%, totally 40 participants (20 per group) will be randomized and allocated each EA or sham acupuncture (SA) group.

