#### 2.6.1. Primary Outcome

The change in TUFS will be primarily evaluated. PPIUS is a self-rated diary reporting time points, frequency of urination, and the intensity of urine urgency in 24 hours. The patient's perception of intensity is scored from 0 (no urgency) to 4 (urgency incontinence). TUFS is calculated using the sum of the PPIUS scores. This scale has been validated to assess the severity of overactive bladder and Lower Urinary Tract Symptoms, combining the symptoms of urgent and frequent urination [20]. The patient will be asked to report the scale for 24 hours at baseline and at the end of the trial, respectively.

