### 2.7. Statistical Analysis

Categorical variables will be presented with frequencies and percentage and analyzed by *χ*
^2^ test or Fisher's exact test for demographic information and adverse events. Continuous variables will be presented with mean ± standard deviation and analyzed by two-sample *t*-test or Mann-Whitney *U*-test for demographic information and effectiveness outcomes, depending on the normality of the baseline distribution. If necessary, efficacy data will be evaluated with analysis of covariance (ANCOVA) with covariates of recruiting center and any demographic information, such as gender.

Full analysis set (FAS) (defined as the data set of the participants who receive 7 or more EA or SA sessions and provide the primary outcome at least once) will be primarily used for the effectiveness assessment. Per-protocol (PP) analysis (defined as the data set of the participants who complete every 10 EA or SA session) will be subordinately adopted. Missing data will be imputed by the last observation carried forward method. For the safety assessment, safety set analysis will be performed with the data obtained from all of the participants who receive at least one EA or SA session.

Finally, for the BI assessment, the distribution of actual allocation and participant's responses (EA group, SA group, or DO NOT KNOW) will be presented with 2 × 3 cross tabulation along with the index calculation.

IBM SPSS Statistics for Windows (Version 21.0. IBM Corp. Released 2012. Armonk, NY, USA) will be used, with 0.05 significance levels by a 2-sided test.

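### TUFS is taken only at baseline and closeout, so last-observation-carried-forward enters zero change for any analysed patient without a closeout score

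*Protocol article*

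**What the plan says.** Section 2.6.1 names the primary outcome: "The change in TUFS will be primarily evaluated". It fixes two measurement times: "The patient will be asked to report the scale for 24 hours at baseline and at the end of the trial, respectively". Table 1 agrees, with TUFS, ICIQ-UI-SF, K-IPSS and the LUTS Outcome Score marked at V2 (Day 0) and V13 (closeout) and at no treatment visit. PPIUS and K-IPSS are also taken at V1, but that is screening, before any session.

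Section 2.7 gives the missing-data rule: "Missing data will be imputed by the last observation carried forward method". It defines the full analysis set (FAS) as "participants who receive 7 or more EA or SA sessions and provide the primary outcome at least once", and this set "will be primarily used for the effectiveness assessment". The per-protocol (PP) set is "defined as the data set of the participants who complete every 10 EA or SA session"; a closeout diary is not among its conditions.

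**The concern.** LOCF needs a value observed after treatment has begun. This schedule has none, so the only value that can be carried to V13 is a pre-treatment one, and the imputed change is zero by construction. The article states this rule outright; it is not a detail left to an analysis plan.

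Zero is not a neutral value here. The Background section cites incontinence prevalence after stroke of 32% to 79% at admission and 25% to 28% at discharge, so improvement without EA is plausible, though less so for patients late in the 2-year eligibility window. Section 2.5.3 also permits conventional incontinence treatment in both arms. A patient who had most of the sessions but returned no closeout diary would be recorded as having not changed at all.

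Two things are at stake: the estimated difference between arms, and the variability estimate. Section 3 says the results will be used to calculate the sample size of a full-scale trial.

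**Working it through.** **Inputs.** Measurement times: V2 and V13 only (section 2.6.1, Table 1). Group size: "Accordingly, we decided that 18 participants per group would be adequate" (section 2.2.4), with 10% dropout and 20 randomised per arm. The article gives no mean change or SD for TUFS, so the values used below are assumptions. Negative means improvement.

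**1. The plan's own figure.** 18 / (1 − 0.10) = 20 per arm, 40 in total. This reproduces and is not affected by the point.

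**2. What LOCF does.** If V13 is missing, V13 is set to V2, so change = V2 − V2 = 0.

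**3. Bias in the difference.** Let m be the share of analysed patients imputed in an arm and μ the mean change those patients would have had. Entering zeros removes m·μ from the arm mean, so

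bias (EA minus SA) = −(mE·μE − mS·μS).

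If the missing patients would have changed like the rest of their arm, the estimate is (1 − mE)·μE − (1 − mS)·μS. With 20 analysed per arm:

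| Assumed change EA / SA | Imputed EA / SA | True difference | LOCF estimate | Bias |
|---|---|---|---|---|
| −6 / −3 | 2 / 2 | −3 | −5.40 + 2.70 = −2.70 | +0.30 |
| −6 / −3 | 3 / 1 | −3 | −5.10 + 2.85 = −2.25 | +0.75 |
| −6 / −3 | 1 / 2 | −3 | −5.70 + 2.70 = −3.00 | 0 |
| −6 / −3 | 1 / 3 | −3 | −5.70 + 2.55 = −3.15 | −0.15 |
| −6 / 0 | 1 / 3 | −6 | −5.70 + 0 = −5.70 | +0.30 |
| −3 / −3 | 4 / 0 | 0 | −2.40 + 3.00 = +0.60 | +0.60 |
| −3 / −3 | 0 / 4 | 0 | −3.00 + 2.40 = −0.60 | −0.60 |

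Equal loss of 2 in 20 shrinks the difference by 0.30 / 3 = 10%. When both arms improve, the bias changes sign at mS/mE = μE/μS. At −6 and −3, SA must have more than twice the imputed share of EA before the effect is inflated. In the two no-effect rows, simulated with an assumed SD of 6, the 5% two-sided t-test rejected in 5.9% (4 / 0) and 6.2% (0 / 4) of trials.

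**4. SD and SE.** With a share m of zeros, the variance of change in an arm becomes (1 − m)σ² + m(1 − m)μ². Take a second set of assumed means, −10 (EA) and −6 (SA), with 2 of 20 imputed per arm, and compare with 18 observed per arm:

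- Assumed SD 4: EA 14.40 + 9.00 = 23.40; SA 14.40 + 3.24 = 17.64. LOCF SE = √(41.04/20) = 1.43; observed SE = √(32/18) = 1.33. LOCF is about 7% larger.
- Assumed SD 10: EA 90 + 9.00 = 99.00; SA 90 + 3.24 = 93.24. LOCF SE = √(192.24/20) = 3.10; observed SE = √(200/18) = 3.33. LOCF is about 7% smaller.

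The SE is distorted either way, and the direction depends on an SD that is not known.

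**5. How many values.** Two imputed per arm (4 of 40) would need the whole planned 10% dropout to fall after session 7. At that dropout rate it is an upper bound.

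**The case against.** The strongest reply is that LOCF may never touch the primary TUFS analysis. The primary outcome is a change between baseline and endpoint, and a baseline diary alone provides no change. Since TUFS is taken at V2, before any session, a condition met by baseline would exclude almost nobody who reached 7 sessions; a post-baseline reading gives the clause a function. On that reading every FAS patient has a V13 diary and nothing is imputed for TUFS. This is a fair reading, but the text does not settle it, and a requirement of at least once is odd for a score with a single post-baseline time. LOCF would in any case still apply to missing secondary scores and, as that set is written, to PP patients without a V13 diary, unless the PP set is meant to lie inside the FAS, which the article does not say.

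The number affected may also be small. V13 shares its Day 18 (±3) window with the end of treatment, and this is a pilot without a powered hypothesis. That limits the severity but does not make the rule sound.

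Three stronger readings that a reader might infer are not supported:

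- *Every missing primary endpoint becomes a zero.* Patients with fewer than 7 sessions are outside the FAS and are not imputed there.
- *The arm that loses more patients sets the direction of bias.* Equal loss is already biased when the arms differ, and heavier SA loss can give no bias (1 / 2 at −6 / −3) or bias toward zero (1 / 3 at −6 / 0). Loss alone decides the sign only when the unobserved mean changes are equal.
- *The SE is about 5% too small.* That figure, √(36/40) = 0.949, assumes an unchanged SD and 4 imputed values. Step 4 shows that the SE can move either way.

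**Conclusion.** The concern holds in bounded form. On this schedule LOCF is baseline carried forward and assigns exactly zero change to any analysed patient without a closeout score. That follows from the article's own text. Whether it reaches the primary TUFS analysis depends on an unclear FAS condition.

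If it does, the difference shrinks by 10% when 10% are imputed in each arm, assuming those patients would have changed like the rest of their arm. Unequal loss may shrink, inflate or create a difference. The bias formula is general; the point values rest on assumed TUFS changes. Neither the direction of the bias nor that of the SE error can be fixed from the document. The article's purpose of sizing a later trial makes the distorted difference and SD worth correcting. Severity: should-fix.

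**What to change.** In section 2.7:

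- Remove LOCF as the primary missing-data rule.
- Analyse observed V13 scores by ANCOVA with the baseline score and centre as covariates. The article at present offers ANCOVA only if needed, and does not name the baseline score as a covariate.
- For an observed-case set, state that the primary-outcome condition means a post-baseline (V13) diary. Say whether the PP set carries the same condition.
- Where V13 values are missing in an analysed set, including the secondary scores, use multiple imputation from arm, centre and baseline scores.
- Keep baseline carried forward only as a named sensitivity analysis.

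The cost is a few sentences and some analysis code. Sample size, visits and patient burden do not change. The downside is slightly fewer analysed values and possibly wider confidence intervals. The 7-session rule is a separate question and need not change to correct this.

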## 3. Discussion

This study protocol is intended to conduct a pilot multicentered, randomized, parallel, sham-controlled trial, evaluating the effectiveness and safety of EA, compared with SA, for PSUI patients. The primary effectiveness will be measured by a patient-reported scale, TUFS, with other outcomes, namely, ICIQ-UI-SF, K-IPSS, and LUTS Outcome Score. The safety will be analyzed with adverse events reporting.

According to a review study on acupuncture for voiding disorders after stroke, CV4, SP6, CV3, and CV6 are the 4 acupoints that have been most used in 16 clinical studies [26]. These acupoints are known to control the kidney or body fluid and can possibly manage bladder problems, according to the literature on Korean traditional medicine [18].

Park sham is a placebo acupuncture that was developed to make patients indistinguishable from those who receive genuine needling [27]. With use of a specially developed guide tube, patients cannot observe the needle penetrating through the skin. We will use this guide tube to blind participants, even in the actual EA group. The validation test for SA has already been performed [28].

We designed this trial as a pilot study because no preceding study exists. With the results, we expect to explore more adequate trial settings and calculate statistically powered sample sizes for a full-scale clinical trial to confirm the effectiveness and safety of EA therapies for UI in stroke survivors.

## Figures and Tables

**Table 1 tab1:** Study schedule with enrollment, interventions, and assessment plan.

	Study period												
	Enrollment	Allocation	Postallocation										Closeout
Visits	V1	V2	V3	V4	V5	V6	V7	V8	V9	V10	V11	V12	V13

Time point	Day (−1)	Day 0	Days 1–18 (±3 days)										Day 18 (±3 days)

Enrollment													
Informed consent	X												
*[Demographic information]*	X												
*[Medical history]*	X												
*[Concomitant medication]*	X												
*[Laboratory test* ^*∗*^ *]*	X												
*[Uroflowmetry & bladder scan]*	X												
*[PPIUS]*	X												
*[K-IPSS]*	X												
*[MMSE-K]*	X												
Eligibility screen	X												
Random allocation		X											

Interventions													
*[Treatment: electroacupuncture]*			⧫	⧫	⧫	⧫	⧫	⧫	⧫	⧫	⧫	⧫	
*[Control: sham acupuncture]*			⧫	⧫	⧫	⧫	⧫	⧫	⧫	⧫	⧫	⧫	

Assessments													
*[PPIUS/TUFS]*		X											X
*[ICIQ-UI-SF]*		X											X
*[K-IPSS]*		X											X
*[LOS]*		X											X
*[Blinding Index]*													X
*[Adverse events]*			X	X	X	X	X	X	X	X	X	X	

This table has been modified from the example template recommended by SPIRIT guideline [9].

^*∗*^Blood test: PSA (prostate specific antigen) test for male participants. Urine test: urinalysis and urine culture for all participants, HCG (human chorionic gonadotropin) test for fertile female participants

MMSE-K: the Korean version of Mini-Mental State Examination; PPIUS: Patient Perception of Intensity of Urgency Scale; TUFS: Total Urgency and Frequency Score; ICIQ-UI-SF: International Consultation on Incontinence Questionnaire for Urinary Incontinence Short Form; K-IPSS: The Korean version of International Prostate Symptom Scale; LOS: Lower urinary track system Outcome Score.
